#### ***Secondary outcomes***

The secondary outcomes were; 1) Prescription of additional antibiotics or steroids due to further exacerbation, 2) need of non-invasive ventilation (NIV) or mechanical ventilation, 3) death from any cause, 4) emergency room visits, 5) visits to the general practitioner, 6) lung function (FEV1, FVC, FEV1% predicted), 7) bed days, 8) health-related quality of life, 9) healthcare costs, 10) applicability, 11) user satisfaction, or 123) adverse events.

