### Collection of data

All patient data were collected in a case record form (CRF) at baseline, during the intervention, at discharge and again at follow-ups 1, 3 and 6 months after discharge.

Data concerning physiological parameters (pulse, temperature, oxygen saturation, FEV1, and FVC) were collected by a project nurse or project physician or by the ordinary staff at the two hospitals during the ward rounds.

Data concerning readmissions, emergency room visits, rehabilitation, ambulatory visits, deaths, additional prescriptions of prednisone or antibiotics during hospitalization, and length of hospital stays were obtained by searching the hospital databases, The Danish National Patient Registry, and the Danish Civil Registration System, and also by asking the patients at the three follow-up visits. The only data that were solely self-reported from the patient and not obtainable in the hospital databases were the health-related quality of life questionnaires and if there had been any visits to the general practitioner due to COPD. The validated health-related quality of life questionnaires used were: the Saint George Respiratory Questionnaire, (SGRQ), the Clinical COPD questionnaire (CCQ), and the EQ-5D questionnaire, a standardized instrument developed by the Euroqol group.

Also, a user satisfaction questionnaire was handed out to patients in the TT group at discharge and to the nurses who engaged with the ‘outmitted’ patients using the telemedical equipment at the hospital.

The patient user satisfaction questionnaire consisted of 29 questions. Of these, 24 questions were presented in a 5-point Likert-scale (1 strongly disagree through 5 strongly agree) and 5 close-ended questions (yes/no). The questionnaire covers the patient experience in different settings such as the daily ward round, acute calls, the equipment use, and the patient’s general experience of the at home admission with telemedicine technology.

The cognitive status of each patient was evaluated in a substudy using a neuropsychological test battery, including verbal learning, memory capacity and attention and was also evaluated by a self-reported questionnaire: the Subjective Cognitive Functioning (SCF). In the substudy, the patient’s functional status was evaluated by the Instrumental Activity of daily living (IADL)questionnaire.

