### Statistics

All analyses will be done using SAS software version 9.3 http://support.sas.com/software/93. Time to readmission after discharge due to an exacerbation will be assessed using a stratified Cox regression to relax the assumptions of proportional hazards. Differences in readmission rate over time will be assessed using multilevel mixed-effects linear regression analysis with unstructured variance matrix where the baseline values of the outcomes are used as covariates. *P* values below 0.05 will be considered significant for the primary outcome, and *P* values below 0.01 will be considered significant for secondary outcomes. Skewed variables will be power transformed if possible; otherwise, the variables will be transformed into dichotomous responses. Missing values will be replaced using multiple imputations [17]. Survival times will be plotted in a Kaplan-Meier survival curve. Differences between the two groups in prescription of additional antibiotics or steroids due to further exacerbation, need of non-invasive ventilation or mechanical ventilation, emergency room visits, visits to the general practitioner, lung function, bed days, and adverse events will be analyzed with an unpaired Student t-test if data are normally distributed or Mann-Whitney test if not. All categorical data will be analyzed with Chi-square test or Fishers exact test as appropriate. For the health-related quality of life scores, differences from baseline, both within and between study groups, and 95% confidence intervals will be calculated. All analyses will be done on the principle of intention to treat.

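### Quality of life is planned as plain differences from baseline, with no baseline covariate and no named between-group test; a baseline-adjusted contrast would be more precise at almost no cost

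*Protocol article*

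**What the plan says.** The Secondary outcomes section lists quality of life as item 8: "8) health-related quality of life, 9) healthcare costs". Under Collection of data the instruments are "the Saint George Respiratory Questionnaire, (SGRQ), the Clinical COPD questionnaire (CCQ), and the EQ-5D questionnaire". Data are recorded at baseline, during the intervention, at discharge and "at follow-ups 1, 3 and 6 months after discharge".

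Four statements in the Statistics section bear on the analysis:

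- For all secondary outcomes, P "values below 0.01 will be considered significant for secondary outcomes".
- A list of secondary outcomes is to be compared by t-test or Mann-Whitney test: extra prescriptions, ventilation, emergency and general practitioner visits, lung function, bed days and adverse events. Quality of life is not on it.
- Baseline values enter as covariates in a mixed-effects model, but the outcome named for that model is the readmission rate.
- For the quality-of-life scores, "differences from baseline, both within and between study groups, and 95% confidence intervals will be calculated".

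**The concern.** The last of these statements is the whole of the analysis stated for quality of life, and it leaves three weak spots.

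1. **Baseline is subtracted, not adjusted for.** A difference in change scores is unbiased under randomization, but it is usually less precise than an analysis with the baseline score as covariate. It also carries any chance baseline imbalance into the result. Only 57 patients were randomized against 175 planned, and the article concedes insufficient power, so precision is scarce.
2. **The 0.01 rule has no named test to act on.** A reader who is given only 95% intervals must work out for themselves whether a result meets the plan's criterion.
3. **Within-group changes stand on the same footing as the between-group comparison.** Patients were recruited within about a day of an acute admission, and discharge required that their condition had improved. Scores should therefore rise in both arms wherever care is given.

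**Working it through.** **Plan's own figure.** There is none for quality of life. The article's one calculation (70 per group, 175 in total) concerns readmission and does not bear on this point.

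**Inputs from the protocol article.** Threshold 0.01 for secondary outcomes and a 95% interval for quality of life (Statistics); three instruments and three follow-up visits (Collection of data); 57 randomized (Results), 1:1 (Randomization).

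**Assumptions.** Two-sided tests; one score per instrument; equal variance at baseline and follow-up (SD = 1); baseline-to-follow-up correlation r from 0.3 to 0.7; a near-equal split of 28 and 29 with no losses; the quality-of-life baseline collected at enrollment, during the exacerbation.

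**Step 1. Precision of the two contrasts.** With k = √(1/28 + 1/29) = 0.265:

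- Change score: SE = k·√(2(1 − r))
- Baseline as covariate: SE = k·√(1 − r²)
- Ratio: √[(1 − r²) / (2(1 − r))] = √[(1 + r)/2]

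| r | SE, change score | SE, adjusted | Ratio |
|---|---|---|---|
| 0.3 | 0.265 × 1.183 = 0.313 | 0.265 × 0.954 = 0.253 | √0.65 = 0.81 |
| 0.7 | 0.265 × 0.775 = 0.205 | 0.265 × 0.714 = 0.189 | √0.85 = 0.92 |

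The ratio does not depend on the sample size. The variance falls by 35% at r = 0.3 (1 − 0.65) and by 15% at r = 0.7 (1 − 0.85).

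**Step 2. Chance baseline imbalance.** With 28 and 29 patients, an imbalance of one standard error in the baseline mean is 0.265 SD. Given an imbalance d, and no treatment effect, the expected difference in change is −(1 − r)·d. At d = 0.265 that is 0.7 × 0.265 = 0.19 SD for r = 0.3 and 0.3 × 0.265 = 0.08 SD for r = 0.7. Adjustment for baseline removes this.

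**Step 3. Interval level against threshold.** A two-sided 95% interval excludes zero when P<0.05; the interval that matches P<0.01 is the 99% one. Its relative width is 2.576/1.960 = 1.31 (1.33 with t on 55 degrees of freedom). The two criteria disagree only for results with P from 0.01 to below 0.05.

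**Step 4. Both changes together.** A 99% interval from the adjusted model, relative to the planned 95% change-score interval, has width 1.314 × 0.806 = 1.06 (r = 0.3) to 1.314 × 0.922 = 1.21 (r = 0.7).

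**Step 5. Within-group output.** Three instruments, three visits and two arms give 3 × 3 × 2 = 18 within-group changes, against 3 × 3 = 9 between-group contrasts. None of the 18 compares the arms.

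**The case against.** **No contradiction.** The 0.01 rule is stated for secondary outcomes without exception, so it covers quality of life. The sentence on quality of life says what will be calculated, not that an interval excluding zero counts as significant. A 95% interval is a conventional statement of precision and can sit beside a stricter test level. This stands.

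A reader might infer that quality of life would be judged at five times the stated error rate (0.05/0.01 = 5). Or they might infer that nine comparisons carry a 37.0% chance of a false signal (1 − 0.95⁹) in place of 8.6% (1 − 0.99⁹). The document does not support either. Both need the interval to be used as the test against the plan's own rule. The second also treats repeated questionnaires in the same patients as independent; they will be positively correlated, so 37.0% is too high even on its own terms.

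**Between-group comparison is planned.** The sentence includes it, and nowhere does the article present a within-group change as evidence for telemedicine. This also stands. The point is only that the two should be clearly ranked.

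**Adjustment may have been intended.** A change-score contrast is valid, a covariate can be left to the full analysis plan, and the same section uses baseline covariates in its mixed model. The wording there may even have been meant for repeated scores, since a readmission rate has no obvious baseline value. But readmission rate is the only outcome it names, and for quality of life the article commits itself to a different quantity. The covariate is therefore a gain in efficiency, not the correction of an invalid analysis.

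**Conclusion.** The point holds as a minor improvement. The planned error rate for quality of life remains 1% and the section is consistent with itself. What it fixes badly is the estimator and the presentation: differences from baseline where the baseline score could serve as a covariate, no between-group test named for the 0.01 rule, and within-group changes given equal standing although the acute baseline makes improvement likely in both arms.

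The precision forgone is a standard error ratio of 0.81 to 0.92, which rests on the assumed correlation of 0.3 to 0.7 and equal variances. If the follow-up variance differs or the correlation lies outside that range, the ratio changes; as r approaches 1 the gain vanishes. The possible distortion from a one-standard-error baseline imbalance is 0.08 to 0.19 SD on the same assumptions, with a near-equal split of 57. That the quality-of-life baseline was taken during the exacerbation follows from when patients were enrolled, but the article does not say so for the questionnaires in particular.

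**What to change.** For SGRQ, CCQ and EQ-5D, estimate the between-group difference at 1, 3 and 6 months from ANCOVA, or from one mixed model over the three visits, with the baseline score as covariate. State that significance rests on that between-group P<0.01. Then either give 99% intervals to match, or keep 95% intervals and label them as descriptive. Present within-group changes as means, with no inference attached.

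The cost is small. No new data are needed, because baseline scores are already required for the planned differences. There is slightly more modelling. If 99% intervals are chosen they are 1.31 times as wide at the same standard error, or about 1.06 to 1.21 times the planned ones once the adjustment is counted. The Abstract says that results were analyzed in 2013, while the Statistics section is in the future tense. If the comparison had already been seen when the change is made, the report should say so.

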### Adverse events

All adverse events and adverse device events that occurred during the 30-day study observation period will be reported in the final paper. An adverse event is defined as any unwanted event happening to the patient during the clinical trial while using the medical equipment or after using the equipment regardless of whether there is a connection between the use of the equipment and the unwanted event or not. A serious adverse event was defined as an event that leads to death, to life threatening damage or disease, to permanent damage to the body, to permanent disability, or to surgical or medical treatment to avoid these serious events. Also events leading to hospital admission or prolongation of the hospital stay were considered serious events. The formal stopping rule was that the study would be stopped after 18 months of inclusion or before if any serious situations occurred that might put a patient’s welfare at risk. This study is a clinical trial concerning telemedical equipment and all adverse events that may or may not be related to the use of the telemedical equipment will be reported in the CRF and in the final report.

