**Figure 1 F1:**
[figure not shown]
**Photo of the telemedicine technology (TT) equipment used in the Virtual Hospital Trial (VHT).** The photo illustrates the TT equipment used in the patients’ homes and consisted of the following items shown in the photo from left to right: The medicine box containing antibiotics, inhalation medicine, corticosteroids and sedatives; the electronic nebulizer used for inhalation medicine; the touch screen with a built-in webcam; the oxygen compressor on the far right standing on the floor;. the spirometer, pulse oximeter, and thermometer in front of the touch screen were used to send physiological measurements every day to the hospital. Also, the patient phone, which is carried by the nurse working in the acute emergency ward, is in front of the touch screen.

##### 

**List of items** Checklist and training program for the TT group

1. Patient can use the “call hospital” button on the finger touch screen

2. Patient can perform an oxygen saturation and pulse measurement on the finger tip

3. Patient can perform a lung function measurement

4. Patient can use the oxygen supply

5. Patient can use the nebulizer and corresponding medicine

6. Patient can perform an “acute” call to the hospital

7. Know when to dial the Danish emergency number 112

Patients in the telemedicine technology group (TT group) were transported to their own home within a maximum of 3 to 4 hours after randomization. Upon arrival at home, all patients were asked to redo the seven-item checklist to ensure that the patients still were able to perform the necessary procedures of self-management using the home-monitoring devices, the medication and the technology. The patients were accompanied home by a nurse or a doctor together with a technician who installed the technology and the equipment, a procedure that normally would last half an hour. All patients kept the equipment until considered ready for discharge, and the equipment was physically removed immediately thereafter.

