#### ***Control group***

The medical treatment in both groups followed a strict standardized treatment program for COPD patients admitted due to an exacerbation (see list of standard treatment´s section).

##### 

**List of standard treatment** Standard medical treatment regime given in the two groups

• Corticosteroids (oral) Prednisolone 37.5 mg × 1 for 10 days

• Antibiotics (oral) amoxicillin and clavulan acid 500 mg × 3 for 7 days

• Beta-2 agonists and anticholinergics (inhalation) fenoterol and ipratropium bromide via nebulizer in specific intervals

• Oxygen therapy (nasal) when needed

• Sedative (oral) levomepromazine 5 mg × 1 only if needed

The patients allocated to the control group were informed that they would be hospitalized as usual, receiving the conventional standard hospital treatment for an exacerbation.

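### The adverse event definition depends on use of the telemedicine equipment, which only one arm receives, yet adverse events are to be compared between arms

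*Protocol article*

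**What the plan says.** The Adverse events section defines an adverse event as "any unwanted event happening to the patient during the clinical trial while using the medical equipment or after using the equipment", and adds that this holds "regardless of whether there is a connection between the use of the equipment and the unwanted event or not". It identifies the equipment in question: "This study is a clinical trial concerning telemedical equipment". It promises to report "All adverse events and adverse device events that occurred during the 30-day study observation period". The definition of a serious adverse event, in the same section, has no equipment condition of its own; it includes events that lead to admission to hospital or to a longer stay.

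The Secondary outcomes section lists "adverse events" as its last item. The Statistics section plans a comparison of the two groups in which "lung function, bed days, and adverse events will be analyzed with an unpaired Student t-test", with a Mann-Whitney test if the data are not normal and a chi-square or Fisher test for categorical data. Secondary outcomes are judged at 0.01, and all analyses follow intention to treat.

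On who has the equipment, the Interventions section says "Patients in the telemedicine technology group (TT group) were transported to their own home", where the equipment was installed and later removed. Control patients were told that "they would be hospitalized as usual, receiving the conventional standard hospital treatment for an exacerbation".

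**The concern.** An outcome compared between randomized groups must be one that a patient in either group can have. Here the definition sets an exposure condition, use of the equipment, that one group meets by allocation and the other does not. If it is applied as written, the control count is zero whatever happens to those patients, and every event in the telemedicine arm counts as excess.

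The trial asks whether patients with an acute exacerbation can be treated at home instead of in hospital, so readers will look to the adverse event table for comparative safety. A difference produced by the definition could be read as harm from home treatment. If control events are counted anyway, the rule in use is not the published one, and a reader cannot tell which rule produced the table.

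**Working it through.** **Step 1: the sections side by side**

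| Element | Protocol article | Consequence |
|---|---|---|
| Exposure condition (Adverse events) | Event during or after use of the equipment | Equipment use is required |
| Causality (Adverse events) | No connection with the equipment is needed | Waives the causal link only; use is still required |
| Which equipment (Adverse events) | Telemedical | Not hospital devices in general |
| Who has it (Experimental group; Ethical considerations) | Installed in the telemedicine patient's home, removed at discharge | Telemedicine arm |
| Control group | Usual hospital admission; no telemedicine equipment described | Condition not met |
| Comparison (Secondary outcomes; Statistics) | Between groups, by intention to treat | Needs an outcome that both arms can have |

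No other section defines an adverse event for control patients. That they never use the equipment is an inference from these sections. The article does not say so in one sentence.

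**Step 2: size under the literal rule**

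The article states no adverse event rate and no power for this outcome, so there is no figure to reproduce. If each arm has true risk p, the expected observed difference is p − 0 = p, when the true difference is zero.

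Inputs for the illustration:
- 57 patients randomized 1:1 (Results and Randomization sections).
- Arm sizes are not given; 29 telemedicine and 28 control are assumed.
- Significance level 0.01 for secondary outcomes (Statistics section).
- Equal true risk of at least one event, assumed at 10% to 50%.
- Control events fixed at 0.

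With x telemedicine patients having an event and none in control, the two-sided Fisher P value is [C(29,x) + C(28,x)] / C(57,x).
- x = 7: (1,560,780 + 1,184,040) / 264,385,836 = 0.0104, not below 0.01.
- x = 8: (4,292,145 + 3,108,105) / 1,652,411,475 = 0.0045, below 0.01.

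Eight telemedicine patients with an event therefore suffice. The chance of a false difference is P(X ≥ 8) with X ~ Binomial(29, p). The last column applies the same test when both arms are counted by one definition.

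| True risk in both arms | Literal definition | One definition for both arms |
|---|---|---|
| 10% | 0.6% | 0.15% |
| 20% | 21.0% | 0.60% |
| 30% | 67.9% | 0.71% |
| 40% | 94.3% | 0.70% |
| 50% | 99.6% | 0.75% |

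With the split reversed (28 telemedicine, 29 control), seven events suffice (P = 0.0045), and the literal column becomes 1.8%, 32.2%, 78.0%, 96.9% and 99.8%.

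**The case against.** The strongest reply is that collection in both arms was plainly intended. The article names adverse events and adverse device events separately, its definition of a serious event does not mention equipment, and it plans a two-group comparison. The Collection of data section describes one case record form for all patients at baseline, during the intervention, at discharge and at 1, 3 and 6 months. It adds hospital databases, national registries and questions at follow-up visits. This stands. A reader might infer that control events were not recorded, or were counted as zero; the article does not support that. Nor does it support the idea that control patients had no means of ascertainment.

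A reader might also infer that the trial's safety comparison fails altogether. It does not. Readmission is the primary outcome, and death from any cause, need of ventilation and emergency room visits are separate secondary outcomes. None of them depends on the adverse event definition.

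The choice of test is not the fault either, since the Statistics section already allows rank and categorical tests. Nor is the seriousness criterion simply one-sided: prolongation of stay covers patients already in hospital. Some asymmetry remains, because a move from home to hospital during the index episode can count as an admission only in the telemedicine arm.

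Finally, the term for the equipment is not formally defined, and control patients may have had spirometry or oximetry in hospital. But the section itself says that the trial concerns telemedical equipment, so this reading does not remove the conflict. Condensation into an article does not explain it either, because the definition and the comparison are both printed and do not fit together.

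**Conclusion.** The point holds as a conflict between a stated definition and a stated comparison. Followed literally, the definition gives no control events by construction and biases the comparison against telemedicine. The direction does not depend on the event rate, but the size does. At 10% risk the false-positive chance stays near the nominal 1% (0.6% or 1.8%, depending on the split). At 20% it is about 21% to 32%, at 30% about 68% to 78%, and at 50% over 99%. These figures rest on assumed arm sizes, equal true risk, strict use of the definition and Fisher's test; they do not describe the trial's data. Because the main harms are captured by other outcomes and common data sources exist, the severity is moderate.

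**What to change.** - Define an adverse event, in both arms, as any unwanted event from randomization to the end of one stated observation period, regardless of equipment use. State where the 30 days begin and end.
- List adverse device events separately, for the telemedicine arm only, outside the between-group comparison.
- Identify events in both arms from the sources already named under Collection of data.
- Compare the proportion of patients with at least one adverse event, and with at least one serious adverse event, by the chi-square or Fisher test already planned. Give a risk difference with its confidence interval.
- Tabulate transfers to hospital during home admission separately, since admission as a seriousness criterion does not apply equally to patients already in hospital.

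The cost is a reworded definition and modest re-coding of control-arm events. No new data source is needed. If control events were already counted by a rule like this, the only change is to print that rule.
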